## Introduction

 Regular physical activity during childhood is promoted by the WHO and governments worldwide to encourage lifelong health.^1 2^ Schools are among the most important settings for creating active environments for young people to help meet global targets to reduce physical inactivity by 15% by 2030.^2^,^4^ Schooling is compulsory for all children in many high-income settings and where most children spend around a third of their weekday waking time. Thus, whole-school approaches to address physical activity have the potential to level health inequalities^5^,^7^ and have been promoted in global health policies including the Global Action Plan on Physical Activity 2018–2030,^2^ Commission on Ending Childhood Obesity^8^ and UNESCO.^9 10^

UK guidelines recommend that children and young people (aged 5–18 years) should engage in at least 60 min of moderate-to-vigorous physical activity per day, of which 30 min should take place during the school day.^11^ Evidence from England suggests that 30% of children aged 5–16 years are physically active for less than 30 min per day.^12^ Furthermore, children aged 5–11 years, those from lower-income households and those from ethnic minority groups are the least physically active.^12^ Hence, a major implementation gap exists between policy recommendations and practice.

In 2021, the WHO published a policy briefing of promoting physical activity through a whole-school approach^13^ and a toolkit^3^ for schools and colleges to encourage children to be physically active. The development of this toolkit was informed by evidence-based interventions for increasing physical activity among children in school settings.^3^ The toolkit recommends six domains to encourage physical activity; these are: (1) quality physical education, (2) active travel, (3) opportunities to be physically active before and after school, (4) opportunities to be physically active at breaks and lunch, (5) active classrooms and (6) inclusive physical activity approaches for those with additional needs. These approaches need to ensure participation of most, if not all, children and the inclusion of those who may face additional barriers to being physically active outside school.^3 4^

The aim of our study is to explore the implementation of physical activity policies based on the WHO’s recommendation of a whole-school approach and to examine associations between a derived active environment score and children’s physical activity, mental health and educational performance.

Our aim is underpinned by the following research questions:

Which of the WHO’s policies and practices are currently implemented by primary schools in Greater London to create a physically active school environment?Do schools with a higher active school environment score have better physical activity, mental health and educational performance among their pupils?How equitable is the level of an active school environment across subgroups of children including those living in deprived areas, minority ethnic groups and those with disabilities?

## Methods and analysis

### Study design

The Health and Activity of Pupils in the Primary Years (HAPPY) study is an observational quasi-experimental study comprising two components involving primary data collection between October 2023 and December 2024 and was conducted simultaneously (figure 1). The data collection is completed and is being processed and cleaned in preparation for the analysis. The first component of the study was a survey of Greater London state-funded primary schools which assessed the implementation of physical activity policies and practices measured against the WHO recommendations. The second component was a cross-sectional study which measured children’s physical activity (using accelerometers), mental health (parent-reported) and educational performance (teacher-reported).

**Figure 1 F1:**
[figure not shown]
Health and Activity of Pupils in the Primary Years study design. ^a^Schools were recruited and children assessed throughout the data collection period; ^b^children aged 7–8 years.

### Study setting and population

Our school survey was distributed to all state-funded primary schools in Greater London (n=1826). For our cross-sectional study, primary schools were recruited to participate, through which we invited children in year three (aged 7–8 years; one of the age groups identified as the least active in the primary school years^12^) and their parent/guardian to participate. All children in year three were eligible for participation, but participation was optional. Completion of both consent (adult) and assent (child) was required to participate in the study. Our target, based on our previous work,^14^ was to recruit up to 1000 children from approximately 40 schools across Greater London.

### Procedure

#### School survey

Details of all state-funded primary schools were derived from a schools database that we created previously^15^ and updated with details to include new schools. All school details are publicly available from the UK government website.^16^ We distributed paper versions of our survey by post (including a freepost envelope to return the completed survey) in November 2023 and sent four reminders by email (January 2024, April 2024 and July 2024) to encourage survey completion; a final reminder, by post, took place in September 2024 (see figure 1). The survey (both by post and email) was addressed for the attention of the head teacher, but any teacher best placed to answer the questions could complete the survey. The survey closed in December 2024.

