#### Cross-sectional study

We worked with the National Institute for Health and Care Research (NIHR) Clinical Research Network and Schools Research Network who supported the recruitment of primary schools across Greater London. We targeted state-funded primary schools only. These schools are local authority maintained schools (academy converter, academy sponsor led, community, foundation, free schools, voluntary aided and voluntary controlled). State-funded primary schools receive funding through their local authority or directly from the government and they must follow a national curriculum (a set of subjects and standards for children to learn the same things).^17^ Schools were initially contacted by email and those providing an expression of interest were contacted by phone to discuss participation. On verbal agreement, schools were sent a consent form and information sheet (and the school survey if applicable). Through participating schools, we invited children and their parent/guardian to take part in the study by distributing a recruitment pack to the children. The recruitment pack contained a cover letter with information about the study (including details about the study team and contact details), a reply slip (for parents to indicate their participation and to provide their contact details), a parent/guardian information sheet, a children’s information sheet, two consent forms (a parent/guardian consent form and an adult consent form) and a child assent form. Obtaining parent/guardian contact details (address, phone number, email address) through the reply slip allowed the study team to contact the parent/guardian directly to follow-up any missing data. The information sheet explained what participation involved and that all data needed to be collected for the child to receive the monetary incentive (£5 voucher) as a thank you. The completed recruitment packs were returned to the school and collected by the study team 1 week after distribution. Those who had completed the reply slips and consent/assent forms were included in the cross-sectional study. All General Data Protection Regulations were followed. Recruitment of schools commenced in October 2024 with the first data collection taking place in January 2024. All data were collected by the end of December 2024.

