### Data collection: cross-sectional study

There was one time point of data collection per school. Children were visited by a study researcher at their school, who provided the children with an explanation of study involvement and what they needed to do (reiterating the information provided in the information sheet that was included in their recruitment packs) and measured the childrens height and bio-impedance. The children were fitted with the wrist-worn accelerometer on their non-dominant wrist and given a data-collection pack to take home that included instructions of how to wear the accelerometer, duration of wear (7 days a week and worn at all times—not to be taken off during the 7-day wear period), what to do if the accelerometer became uncomfortable to wear and how to contact the study team if the accelerometer was damaged or lost. The recruitment packs also included a paper version of the parent/guardian and child questionnaires (questionnaires were also available to complete online via a link/quick response (QR) code). The front of the pack included the date on which the child should take off the accelerometer and return the accelerometer and completed questionnaires back to the school. The class teachers of participating children were given a questionnaire (paper version) to complete about each participating child’s educational performance. Accelerometers and all questionnaires were collected from the school by the study researcher. Each child who returned their accelerometer and completed questionnaires received a certificate and monetary incentive (Amazon voucher). The study researcher followed up directly with the parent for any accelerometers that were not returned and/or incomplete questionnaires.

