#### School survey

Based on the WHO’s six domains of a whole-school physical activity approach (figure 2),^3^ we consulted with teachers to identify schools’ current practices and policies that support a physically active learning environment. We extracted relevant questions from previous studies of children’s physical activity, including SPEEDY,^18^ WAVES^19^ and GoActive,^20 21^ to capture whether schools support the delivery of a whole-school approach. We piloted the survey by asking primary school teachers to provide feedback on flow, response options, language, ease of understanding and the duration of completion. Any changes were reviewed and agreed by the authors and teachers. Two formats of our survey were created, an online version (using Qualtrics software) accessible via a link or QR code and a paper-based version (online supplemental file 2). Based on the responses from the survey, we will derive an ‘Active Environment Score’ for each school.

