#### Educational performance

Teachers rated each participating child’s ability for reading, writing and mathematics on a 5-point Likert scale ranging from 1 (below expected levels) to 5 (above expected levels).^30^ Ratings are based on the UK’s National Curriculum’s ‘age-related expectations’ which are the standard expectations defined by threshold descriptors indicating the level pupils should be achieving by the end of primary school.^31^ Teachers also rated the child’s concentration and focus in class using a 5-point Likert scale where scores ranged from 0 (never has difficulties) to 4 (always has difficulties).

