### Statistical analysis

All data collection for the study has been completed. The data are being processed and cleaned in preparation for the analysis. We will characterise features of our study population including child sex, ethnicity and adiposity. We will report characteristics of schools including school size, ethnic mix, Ofsted rating, percentage eligible for free school meals and area-based deprivation. We will present school and pupil level baseline characteristics by active environment scores with summary measures (totals, percentages, means and SD, medians and IQRs as appropriate).

The main analysis will treat the main outcome (physical activity during the school day) as a continuous variable. Decisions on valid accelerometer data to include in the analysis will be made when reviewing the data. We will use mixed-effects regression models to estimate the association between physical activity acceleration and the active school environment score. We will include pupil-level covariates (sex, ethnicity) and account for clustering at the school level by including random effects. Covariates will be included in the model in stages to assess how much each contributes to diluting or increasing the effect. To measure equity, the primary analysis will adjust for pre-specified school characteristics including school size, pupils eligible for free school meals, pupils whose first language is not English, children with Special Educational Needs and Disabilities and area-level deprivation. Sensitivity analysis will include clustering at the class-level within the school.

Results will be reported with a 95% CI. Mixed effects regression models as described for physical activity will be repeated for the outcomes of mental health and educational performance. All analyses will be carried out using Stata v18.5 and R statistical software. We will report our findings in line with the Strengthening the Reporting of Observational Studies in Epidemiology^33^ and Logical Explanations & Visualizations of Estimates in Linear mixed models guidelines^34^ for reporting cross-sectional studies.

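### In some schools one teacher may supply both the Active Environment Score and the pupils' education ratings; how often is not documented, so the overlap should be counted and tested before analysis

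*Protocol article*

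**What the plan says.** **Exposure.** In the protocol article, Procedure, School survey, the survey "was addressed for the attention of the head teacher", with the allowance that "any teacher best placed to answer the questions could complete the survey". Under Outcomes and measures, School survey: "Based on the responses from the survey, we will derive an" Active Environment Score for each school. Procedure, Cross-sectional study, adds that schools agreeing to take part in the pupil study were also sent the survey where applicable.

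**Education outcome.** Data collection: cross-sectional study states: "The class teachers of participating children were given a questionnaire (paper version) to complete about each participating child’s educational performance". Under Educational performance, reading, writing and mathematics are each scored 1 to 5, with 5 the best, against age-related expectations. Concentration is scored 0 to 4, with 4 meaning constant difficulty.

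**Analysis.** Statistical analysis repeats the physical activity mixed model for education. The one sensitivity analysis it names is: "Sensitivity analysis will include clustering at the class-level within the school".

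**Limitations.** The discussion names the cross-sectional design and the representativeness of schools; the summary box adds low survey response. Self-report bias is mentioned only as something the accelerometer avoids.

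**The concern.** The allowance for any teacher to answer the survey does not exclude year-three class teachers, who are the people rating the pupils. Where the two roles coincide, exposure and outcome share a source. A teacher inclined to describe things favourably may report more activity provision and also rate pupils more favourably. That would raise the school's score and the reading, writing and mathematics ratings together. For concentration it would lower the number, because higher values mean more difficulties, but the shift is again towards a favourable picture.

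Such a bias lies along the exposure. The repeated mixed model would report it as an association between school environment and education, which is part of the second research question. A class-level random effect changes the variance structure but cannot remove an error correlated with the score.

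**Working it through.** The article gives no figure on this point to reproduce. The check asks how large an association a shared rater could create when the true association is zero.

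**Inputs from the article.** The Sample size section uses 600 pupils in 20 schools, 30 per school. Study setting and population gives a target of up to 1000 children in about 40 schools: 1000/40 = 25 per school.

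**Assumed inputs (none is in the article).**
- s = 0.30: share of score variance due to the respondent's reporting tendency.
- r = 0.10: share of rating variance due to the rater.
- ρ: correlation between the two tendencies in one person.
- p: proportion of schools where the survey respondent is also a rater.
- c: number of raters (classes) per school, at most one of them shared.

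**Expected spurious slope**, in pupil SDs of rating per SD of score:

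b = p · ρ · √(s · r) / c

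With p = 1, ρ = 0.5, c = 1: b = 0.5 × √0.03 = 0.5 × 0.173 = 0.087. At p = 0.5 this halves to 0.043, and at p = 0.25 it is 0.022. With c = 2 and p = 1 it is 0.043.

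**Comparison with sampling error.** For c = 1 the variance of a school mean is r + (1 − r)/n.
- 20 schools of 30: 0.10 + 0.90/30 = 0.130, SD 0.361, SE of slope about 0.361/√19 = 0.083. At full overlap, bias/SE = 0.087/0.083 ≈ 1.05.
- 40 schools of 25: 0.10 + 0.90/25 = 0.136, SD 0.369, SE about 0.369/√39 = 0.059. Bias/SE = 0.087/0.059 ≈ 1.47.

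At a fixed proportion of overlap, more schools shrink the SE but not the bias.

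**Monte Carlo check** (20,000 replicates per cell, school-level regression, two-sided 5% t test, true association zero). Simulated mean slopes match the formula: 0.086 and 0.087 at p = 1, ρ = 0.5, c = 1. With p = 0 or ρ = 0 the rejection rate stays between 4.7% and 5.4%. Otherwise the false-positive rates (%) are:

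| Schools × pupils | Raters per school | ρ | 25% overlap | 50% overlap | 100% overlap |
|---|---|---|---|---|---|
| 20 × 30 | 1 | 0.5 | 5.7 | 8.3 | 17.3 |
| 20 × 30 | 1 | 0.8 | 7.5 | 13.6 | 39.8 |
| 20 × 30 | 2 | 0.5 | 5.4 | 6.1 | 9.5 |
| 20 × 30 | 2 | 0.8 | 5.8 | 8.3 | 18.5 |
| 40 × 25 | 1 | 0.5 | 6.6 | 11.2 | 31.8 |
| 40 × 25 | 1 | 0.8 | 9.1 | 22.6 | 68.4 |
| 40 × 25 | 2 | 0.5 | 5.6 | 7.4 | 14.9 |
| 40 × 25 | 2 | 0.8 | 6.6 | 11.3 | 32.1 |

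The test is two-sided, so the rates apply equally to concentration, with the sign of the slope reversed.

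**The case against.** Overlap is permitted, not demonstrated. The head teacher is the default addressee, and a class teacher answering is the fallback. The survey asks about practices and policies, and the attainment ratings are tied to curriculum expectations, so it is not evident that one trait drives both. Planning a class-level analysis suggests that at least some schools have several classes, which dilutes the effect. The survey form and the supplementary description of measures are not at hand and may record the respondent's role, and a sensitivity analysis of this kind could sit in a statistical analysis plan. The article also limits its claims to association.

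Most of this stands, and it bounds the size of the point. It does not remove it: the respondent rule and the assignment of raters are both stated, together they allow one source for exposure and outcome, and the one sensitivity analysis named does not address that. Class clustering is not offered as a remedy for rater bias, so the authors should not be faulted as if it were.

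A reader might go further and infer that a score-education association could not be told apart from rater bias at all. One might reason that if a single leniency trait explains a share v of the variance in both score and school-mean rating, the spurious correlation equals v, or 0.1 to 0.3 for v of 10% to 30%. That algebra is correct but is a ceiling: it needs the same person in both roles in every school, rating every pupil, with one identical trait behind both. Nothing in the article supports those conditions.

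**Conclusion.** The point holds as a limited one. The arrangement allows one teacher to supply both exposure and education outcome, and the frequency is unknown. At ρ = 0.5 and overlap of 25% to 50%, the false-positive rate is 5.4% to 8.3% with 20 schools and 5.6% to 11.2% with 40, against a nominal 5%. It becomes material only when overlap is common and the tendencies are clearly correlated. All of this rests on the assumed s, r, ρ and p.

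It would be wrong to conclude that overlap occurred, or that rating teachers in general knew the exposure. The article is silent on masking. A teacher who did both tasks would know their own survey answers but not the derived score. Only the teacher-rated education outcomes, which are secondary, are exposed; the accelerometer primary outcome and the parent-reported SDQ are not. This is an inexpensive improvement, not a flaw in the main analysis.

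**What to change.** Data collection is finished but analysis has not begun, so the following can still be fixed in advance:

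1. For each cross-sectional school, establish whether the survey respondent also rated pupils, from the survey form if it records this or otherwise by a short query. Report the number of schools and pupils concerned.
2. Pre-state a sensitivity analysis that repeats the education models without pupils rated by the survey respondent. Set its estimate and 95% CI beside those of the main model. Do not make the conclusion depend on whether significance survives: the score varies only between some 20 to 40 schools, and a smaller, selected subset can lose significance through imprecision alone.
3. State as a limitation that the exposure and the education outcomes are both reported by school staff, and note the reversed direction of the concentration item when describing likely bias.

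The cost is one indicator variable, at most about 20 to 40 brief queries, one rerun of the education models and a sentence or two of text. The drawback is wider intervals in that rerun. The main analyses are unchanged.

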#### Cross-sectional study

We worked with the National Institute for Health and Care Research (NIHR) Clinical Research Network and Schools Research Network who supported the recruitment of primary schools across Greater London. We targeted state-funded primary schools only. These schools are local authority maintained schools (academy converter, academy sponsor led, community, foundation, free schools, voluntary aided and voluntary controlled). State-funded primary schools receive funding through their local authority or directly from the government and they must follow a national curriculum (a set of subjects and standards for children to learn the same things).^17^ Schools were initially contacted by email and those providing an expression of interest were contacted by phone to discuss participation. On verbal agreement, schools were sent a consent form and information sheet (and the school survey if applicable). Through participating schools, we invited children and their parent/guardian to take part in the study by distributing a recruitment pack to the children. The recruitment pack contained a cover letter with information about the study (including details about the study team and contact details), a reply slip (for parents to indicate their participation and to provide their contact details), a parent/guardian information sheet, a children’s information sheet, two consent forms (a parent/guardian consent form and an adult consent form) and a child assent form. Obtaining parent/guardian contact details (address, phone number, email address) through the reply slip allowed the study team to contact the parent/guardian directly to follow-up any missing data. The information sheet explained what participation involved and that all data needed to be collected for the child to receive the monetary incentive (£5 voucher) as a thank you. The completed recruitment packs were returned to the school and collected by the study team 1 week after distribution. Those who had completed the reply slips and consent/assent forms were included in the cross-sectional study. All General Data Protection Regulations were followed. Recruitment of schools commenced in October 2024 with the first data collection taking place in January 2024. All data were collected by the end of December 2024.

